### Interventions and control

Participants in the device intervention arms are provided with an electrical stimulator system, (Fig. 1) to use every day for 60 min, for the 6-week intervention period. The system consists of a small box containing the stimulator electronics (ShefStim APS), linked to a flexible array of 64 electrodes (arranged as 8 rows by 8 columns), overlaid with a bespoke biocompatible patterned hydrogel layer (SEKISUI ST-GEL, NR-SO320/100, SEKISUI KASEI CO.LTD.), worn over the upper arm with a bespoke flexible sleeve. It sends electrical impulses via the array of 64 individually controllable electrodes.

**Fig. 1 Fig1:**
[figure not shown]
ShefStim APS Stimulator with connected electrode array (**a**). SHAPES system applied to the upper arm (Shefstim APS stimulator box in yellow, electrode array in green, arm sleeve in blue) (**b**)

Although programming of each electrode is fully flexible, for this study the two configurations are:

#### TENS

The central 16 array electrodes (4 × 4) are activated simultaneously with a 1s rising edge ramp building up to 4s of stimulation at a pulse repetition frequency of 100 Hz and with a pulse width of 250µs, followed by a 1s falling edge ramp and then a 4s off period. The stimulation pattern is then repeated.

#### SHAPES

Each horizontal row of 8 electrodes on the array is sequentially activated for 0.3s at a pulse repetition frequency of 50 Hz and with a pulse width of 250µs. After all 8 rows of electrodes have operated the stimulation pauses for 2.5s before the sequence is repeated.

The participants in the usual care arm do not receive any device. The systems are programmed following randomisation allocation, using a QR code that is scanned onto a stimulator remote control (repurposed Alcatel 1c smartphone) and delivered via Bluetooth LE to the stimulator box. The participant’s mid-bicep circumference is be measured and the oversized sleeve cut to size to ensure that a personalised sleeve fit is achieved. When applied, the biocompatible hydrogel layer should contact the skin overlying the extensor aspect of the affected upper limb, over the triceps area. During the setup of the ShefStim APS (for those in the SHAPES or TENS arms of the study) the stimulation intensity (current) is gradually increased until the underlying muscle begins to twitch (motor threshold, MT). If the participant experiences any discomfort from the stimulation, the intensity is limited to the highest that is comfortable for them. The stimulation level is then set to 90% of the MT or, if the MT was not reached, 90% of the maximum comfortable level. This intensity is recorded at baseline and becomes the default level for home use. Participants are trained on how to apply the sleeve and, if necessary, adjust the stimulation intensities (within clinically set levels) for comfort.

During the intervention participants can receive all usual cares for spasticity management provided by the NHS (e.g. botulinum toxin, oral agents, stretching exercises etc.). This will be recorded and compared between the 3 groups and adjusted for in the statistical analysis.

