At the second study visit, other baseline outcome measures are completed. Participants in the SHAPES or TENS arms receive a specially designed upper limb electrical stimulation system (ShefStim APS) and are trained on how to apply and use the device each day during the intervention period. All devices are configured to the allocated TENS or SHAPES arms of the study using a QR code to maintain blinding. Participants then deliver the intervention at home independently or with the help of a care giver for 6 weeks. After 2–3 weeks all participants are contacted to check that they are managing the NRS-S diary, with those in the device arms also receive a safety / device review with the study team. At the end of the 6-week intervention period they return for end of treatment outcome measures that also include an assessment of healthcare utilisation. These assessments are repeated at 6 weeks, 12 weeks and 24 weeks after the end of intervention period. All participants are invited to undergo experiential interviews, providing qualitative data on intervention use. While participants and clinicians facilitating the treatment checks will not be blinded to the control group, outcome measures will be undertaken by researchers blinded to treatment allocation, while all participants and researchers undertaking outcome measure assessments will be blinded to type of electrical stimulation.

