### Outcome measures

Clinical examinations of outcome measures are highlighted in Table 2, are collected at baseline, end of treatment (6 weeks), and then 6, 12 and 24 weeks after the end of treatment. These are performed by clinicians with appropriate experience in their application. The primary outcome measure is the.

**Table 2 Tab2:** Study Outcome Measures

**Primary outcome measure** (End of treatment – 6 weeks)	Mean NRS for 7 days.
**Secondary outcome measures**	MAS
	MRC
	Leeds Arm Spasticity Impact Scale
	ARAT
	EQoL 5D-5 L
	SQoL − 6

averaged 7-day NRS-S. This is a simple patient reported level of elbow spasticity where 0 = no spasticity and 10 = worst possible spasticity. This is recorded daily either on paper report forms or digitally according to patient preference. Its validity and reliability in stroke is established as is the minimally important clinical difference (MCID) [18]. Through co-design we have adapted the NRS-S to enable easier completion amongst those with cognitive impairment and aphasia (Fig. 2). The MCID for the NRS-S is a change of ≥ 18% (i.e. 2 points) from baseline to follow up assessment. ^17^ The primary endpoint for this study is the proportion of participants experiencing this MCID improvement in each group. Averaged 7-day NRS-S is calculated at baseline, end of intervention (6 weeks), and then at 6 weeks, 12 weeks and 24 weeks after the end of intervention (Fig. 3).

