### Statistical analysis and sample size

Study analysis will be conducted on an intention to treat basis. Baseline characteristics will be presented by treatment group. Summary statistics for each of the endpoints will be reported at each available time point (baseline, EOT, and 6, 12 and 24 weeks after end of treatment). Results will be reported with confidence interval where relevant, for example, in reporting the average difference between treatments in the secondary endpoints. We previously carried out a community-based study using the NRS-S as an outcome measure [16]. Analysis of data from the study was used for the sample size calculation. A change in average NRS-S of 18% from baseline to follow-up time point (MCID) is considered a success. The proportion of successes will be compared between groups (pairwise).

A parallel gatekeeper design has been developed such that the first two significance tests share the total *p*-value equally (each tested at 0.025 level). This will be split equally between the first primary objective (SHAPES vs. usual care, and TENS vs. usual care at EOT (6 weeks) using 2.5% significance each). If one or both of these tests are significant then the *p*-value will be reutilised for testing the second primary objective (SHAPES vs. TENS at EOT and 6 weeks after EOT). This will utilise Chi-squared test (or an exact test if required). Between group efficacy at follow up timepoints (3 and 6 month) will also utilise a continuity corrected Chi-squared test.

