We calculated the sample size using data from our previous study [15]. The sample size calculation for a two group t-test for equal means showed that to conduct a three arm randomized control trial of SHAPES, TENS and ‘usual care’ control, we would need 66 subjects per group (total 198 participants) to have 90% power to demonstrate a MCID reduction of 18% in NRS at the 1% significance level to allow for multiple testing. In our feasibility study 67% of participants showed good adherence with the intervention and 73% with recording of NRS. We will recruit a total of 297 patients with PSES to the study who are being randomised to one of the 3 arms. We aim to achieve a minimum of 66 participants to adhere to and complete the protocol in each group with good adherence to the intervention schedule and a minimum of 4 of 7 daily NRS-S recording. This will be known as the Per Protocol Set (PPS). Sensitivity analyses will be conducted to investigate the impact of missing or incomplete data, non-compliance, and spasticity severity. The sample size calculation was done in R using simulations.

Analysis of other secondary objectives (ARAT, MAS, MRC, LASIS, EQ-5D, SQoL-6D) will use repeated measures analysis with treatment group and timepoint as factors, baseline as a covariate and subject as a random effect to investigate the within-participant change in each outcome over time and to see if there is a treatment effect. As some of these outcomes are ordinal, it may not be possible to satisfy the conditions of a repeated measures ANOVA thus Friedman test may be used instead with pairwise Wilcoxon Signed Rank tests for any post-hoc analysis requirements. Since these analyses are exploratory, no adjustment for multiplicity will be made – nor will significant conclusions be drawn.

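### The plan promises to adjust for spasticity treatments received after randomisation; this departs from intention to treat, is liable to bias, and matches no analysis the protocol describes

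*Protocol article*

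**What the plan says.** In the protocol article, under Interventions and control (end of the SHAPES subsection): "During the intervention participants can receive all usual cares for spasticity management provided by the NHS". Botulinum toxin, oral drugs and stretching are given as examples. The next sentence commits to handling this care in the analysis: "This will be recorded and compared between the 3 groups and adjusted for in the statistical analysis". It names no model, endpoint or estimand.

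Under Statistical analysis and sample size: "Study analysis will be conducted on an intention to treat basis". The endpoint is binary (Outcome measures): "The primary endpoint for this study is the proportion of participants experiencing this MCID improvement in each group". For the primary comparisons: "This will utilise Chi-squared test (or an exact test if required"). For later time points: "Between group efficacy at follow up timepoints (3 and 6 month) will also utilise a continuity corrected Chi-squared test". The other secondary outcomes use "repeated measures analysis with treatment group and timepoint as factors, baseline as a covariate and subject as a random effect", with Friedman and Wilcoxon tests as the fallback. The listed sensitivity analyses cover missing data, non-compliance and spasticity severity; co-treatment is not among them.

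On blinding (Study procedures): "participants and clinicians facilitating the treatment checks will not be blinded to the control group". Type of stimulation is blinded between the two device arms.

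**The concern.** Care received during the intervention is measured after allocation and can depend on it in two ways. Its use may follow the course of spasticity, which the device is meant to change. Participants in the usual care arm also know they have no device, and may seek or be offered more of other things. Holding such a variable fixed removes whatever part of the arm difference runs through co-treatment. It also opens a path through unmeasured severity, which can drive both co-treatment and outcome. The result no longer estimates the intention-to-treat difference.

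There is a second problem of consistency. The protocol promises an adjustment that none of its described analyses performs. A team could report the plain chi-squared result or an adjusted one and cite the protocol for either. The device versus usual care tests, each at 0.025, also open the gate to SHAPES versus TENS, so this freedom reaches both primary objectives.

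**Working it through.** **Arm size.** The plan's total reproduces: 66 / 0.67 = 98.5, rounded up to 99 per arm, and 3 × 99 = 297. The point does not depend on this figure; 99 per arm and the first-stage level of 0.025 are used below for rejection rates.

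**Is the adjustment in any stated analysis?**
- Primary comparisons: plain chi-squared or exact test of two proportions; no covariate.
- Later time points: continuity-corrected chi-squared test; no covariate.
- Secondary outcomes: treatment, time point, baseline and subject; no co-treatment term. The Friedman/Wilcoxon fallback carries none either.
- Sensitivity analyses: co-treatment not listed.

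**What would adjustment do?** The documents give no co-treatment rates or effects, so every input here is an assumption. The log-odds of success are -0.85 + 0.9 × device + 1.0 × co-treatment. The adjusted estimate is the Mantel-Haenszel risk difference over co-treatment strata, with weight w = n1·n0/(n1 + n0).

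Case (b), by hand: co-treatment in 40% of controls and 15% of the device arm, with no shared cause.
- Success without co-treatment: control 0.299, device 0.512 (difference 0.213).
- Success with co-treatment: control 0.537, device 0.741 (difference 0.203).
- Control overall: 0.60 × 0.299 + 0.40 × 0.537 = 0.395.
- Device overall: 0.85 × 0.512 + 0.15 × 0.741 = 0.547.
- Intention-to-treat difference: 0.547 - 0.395 = 0.152.
- Weights: 0.60 × 0.85 / 1.45 = 0.352 and 0.40 × 0.15 / 0.55 = 0.109.
- Adjusted difference: (0.352 × 0.213 + 0.109 × 0.203) / 0.461 = 0.211.

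The other cases add a standard normal severity term that raises the log-odds of co-treatment by 0.8 per SD and lowers the log-odds of success by 1.0 per SD. Risk differences come from simulation of 1,000,000 per arm; rejection rates come from 3,000 trials of 99 per arm, using an uncorrected chi-squared test against a Cochran-Mantel-Haenszel test.

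| Case | Co-treatment, control / device | ITT difference | Adjusted difference | Rejection, unadjusted / adjusted |
|---|---|---|---|---|
| (a) no device effect, inert co-treatment | 41% / 18% | 0.000 | -0.030 | 2.1% / 3.6% |
| (b) device effect, no shared cause | 40% / 15% | 0.152 | 0.211 | 48% / 76% |
| (c) device effect, severity shared | 41% / 18% | 0.139 | 0.152 | 39% / 42% |
| (d) as (c), smaller imbalance | 23% / 12% | 0.162 | 0.168 | 53% / 54% |
| (e) as (c), equal use | 23% / 23% | 0.186 | 0.186 | 66% / 65% |

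A separate illustration on a continuous scale moves towards the null. It assumes a device effect of -0.5 SD on mid-course spasticity, toxin use driven by that spasticity (19% usual care, 13% device), and a toxin effect of -0.4 SD. The randomised contrast is -0.5 + (0.13 - 0.19) × (-0.4) = -0.476 (simulated -0.477); adjusted for toxin use it is -0.437. The attenuation arises because toxin use stands in for the mid-course spasticity that the device has changed.

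So the shift can be nil, favour the device or go against it, depending on quantities the documents do not give.

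**The case against.** The strongest reply is that the plan is already safe. If the plain chi-squared or exact test is run as written, the primary result is the unadjusted intention-to-treat contrast. The adjustment sentence refers only to the statistical analysis in general, and an adjusted supportive analysis could sit beside the primary test, with details left to an analysis plan that is not shown. A stratified form of the chi-squared test could also carry the covariate. All of this stands. A reader might infer that the sentence breaks the randomised comparison for the primary objective, or that the two sections can never be followed together. The documents do not support that: the damage occurs only if the adjustment is applied to the primary comparison.

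It is also fair that bias needs co-treatment to differ by arm (case (e) shows no shift with equal use), and that imbalance is not established. Six weeks is short, the protocol's introduction says toxin can take several weeks to act, and the unblinded clinicians mentioned are those doing treatment checks, not necessarily those who prescribe. Some of the care will have continued from baseline. For SHAPES versus TENS, blinding closes the route through knowledge of allocation, though not the route through a differing course of spasticity.

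What the reply does not remove is that the sentence is a positive commitment, for a variable that may respond to arm, without saying which analysis it governs. That is a conflict in the text rather than a detail left open.

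**Conclusion.** The point holds in this form: the commitment to adjust for spasticity care received during the intervention departs from the stated intention-to-treat comparison, is liable to bias the effect in either direction, and conflicts with the analyses described. It bears mainly on SHAPES versus usual care and TENS versus usual care.

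The size cannot be known in advance. The shifts shown, from 0.00 to +0.06 in risk difference with a device effect and -0.03 without one, rest wholly on assumed rates and effects; they illustrate and do not predict. It would go too far to say that the trial's estimate is biased, or that adjustment always removes part of the effect: with equal use nothing shifts, and case (b) inflates the difference. The inconsistency, and the choice it leaves between an adjusted and an unadjusted primary result, stands whatever the rates turn out to be.

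**What to change.** - In Interventions and control, remove the commitment to adjust for treatments received after randomisation. Keep the recording of that care and its descriptive comparison by arm.
- In Statistical analysis and sample size, state that the primary comparison is the treatment-policy (intention-to-treat) contrast, whatever other spasticity care was received. Make it unadjusted, or adjusted only for baseline variables such as baseline 7-day NRS-S and anti-spasticity treatment at baseline. If baseline adjustment is chosen, name a method that can carry it in place of the plain test.
- Confine any co-treatment analysis to a labelled sensitivity analysis with a stated estimand. Counting participants who start botulinum toxin as non-responders, if used, should be labelled a composite strategy. It does not estimate the effect without extra treatment, and it would favour the device arms if controls start toxin more often.

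The cost is a few sentences and at most one sensitivity analysis. No extra data are needed: co-treatment is already to be recorded, and the baseline healthcare utilisation assessment covers medication use. No figure in the protocol changes.

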### Outcome measures

Clinical examinations of outcome measures are highlighted in Table 2, are collected at baseline, end of treatment (6 weeks), and then 6, 12 and 24 weeks after the end of treatment. These are performed by clinicians with appropriate experience in their application. The primary outcome measure is the.

**Table 2 Tab2:** Study Outcome Measures

**Primary outcome measure** (End of treatment – 6 weeks)	Mean NRS for 7 days.
**Secondary outcome measures**	MAS
	MRC
	Leeds Arm Spasticity Impact Scale
	ARAT
	EQoL 5D-5 L
	SQoL − 6

averaged 7-day NRS-S. This is a simple patient reported level of elbow spasticity where 0 = no spasticity and 10 = worst possible spasticity. This is recorded daily either on paper report forms or digitally according to patient preference. Its validity and reliability in stroke is established as is the minimally important clinical difference (MCID) [18]. Through co-design we have adapted the NRS-S to enable easier completion amongst those with cognitive impairment and aphasia (Fig. 2). The MCID for the NRS-S is a change of ≥ 18% (i.e. 2 points) from baseline to follow up assessment. ^17^ The primary endpoint for this study is the proportion of participants experiencing this MCID improvement in each group. Averaged 7-day NRS-S is calculated at baseline, end of intervention (6 weeks), and then at 6 weeks, 12 weeks and 24 weeks after the end of intervention (Fig. 3).

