### Study objectives

#### Primary objectives

To determine whether SHAPES and/or TENS interventions lead to a greater proportion of participants with PSES experiencing meaningful improvements in spasticity (NRS-S change > 18% compared to usual care) after 6 weeks of treatment.To determine whether the SHAPES intervention leads to a greater proportion of participants with PSES experiencing meaningful improvements in spasticity compared to TENS after 6 weeks of treatment.

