## Methods and design

### Design

A partially blind, multi-site, 3-arm randomised control trial, evaluating the change in elbow spasticity after six weeks of intervention measured by NRS-S and with the key outcome of interest being the proportion in each group that achieve an improvement of 18% in 7-day average NRS-S between the two time points. The investigation compares the efficacy of the SHAPES stimulation to TENS stimulation and both compared to usual care at different time points.

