**Inclusion Criteria**
1. Age 18 to 100 years
2. 2-26 weeks after stroke
3. Weakness of elbow extension of MRC grade 4 or below
4. Spasticity of elbow, of grade-1 or more on the Modified Ashworth Scale (MAS) of elbow flexion

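### The primary responder threshold equates 18% with 2 points, which are not equal on a 0–10 scale, and the denominator of the 18% is never stated

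*Protocol article*

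**What the plan says.** The Outcome measures section describes the NRS-S as a patient-reported rating "where 0 = no spasticity and 10 = worst possible spasticity". It then sets the minimal important difference at a change of at least "18% (i.e. 2 points) from baseline to follow up assessment". The primary endpoint is tied directly to that threshold: "The primary endpoint for this study is the proportion of participants experiencing this MCID improvement in each group".

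Elsewhere the threshold appears only as a percentage:

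- **Abstract:** 18%, with no points value.
- **Primary objectives:** strictly more than 18%, in a bracket ending "18% compared to usual care) after 6 weeks of treatment".
- **Design:** "an improvement of 18% in 7-day average NRS-S between the two time points".
- **Statistical analysis and sample size:** "A change in average NRS-S of 18% from baseline to follow-up time point (MCID) is considered a success".

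Under Study procedures, the baseline score is the average of at least four of seven daily ratings. The listed eligibility criteria set spasticity severity by clinical grade ("Spasticity of elbow, of grade-1 or more on the Modified Ashworth Scale (MAS) of elbow flexion") and give no minimum NRS-S.

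**The concern.** The sentence that defines the primary endpoint presents a percentage and a points value as the same thing. If they differ, a participant can be a responder under one and a non-responder under the other, and the protocol could be cited for either classification. The confirmatory tests compare proportions of responders between arms, so the threshold feeds directly into the usual-care rate and the between-arm difference.

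The percentage also has two ordinary readings: a share of the individual's baseline, or a share of the 0–10 range. No section says which is meant. The inequality differs too: at least 18% in Outcome measures, more than 18% in the Primary objectives.

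**Working it through.** **1. Does 18% equal 2 points?** Inputs: scale 0 to 10, threshold 18%, gloss 2 points (all from Outcome measures).

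- As a share of baseline b, the required fall is 0.18 × b. It equals 2 only at b = 2 / 0.18 = 11.1, which is off the scale.
- As a share of the scale range, 0.18 × 10 = 1.8 points.
- Counting the 11 response categories instead, 0.18 × 11 = 1.98 points.

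| Baseline | Fall needed, 18% of baseline | 2 points as % of baseline |
|---|---|---|
| 2 | 0.36 | 100% |
| 4 | 0.72 | 50% |
| 5 | 0.90 | 40% |
| 6 | 1.08 | 33% |
| 8 | 1.44 | 25% |
| 10 | 1.80 | 20% |

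The 2-point rule is stricter at every possible baseline, and nobody with a baseline below 2 can meet it.

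**2. Does rounding 1.8 to 2 make the difference harmless?** Not fully. With seven ratings at each time point the change moves in steps of 1/7. A fall of 13/7 = 1.857 passes 1.8 and fails 2.

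**3. How far does the choice move the responder rate?** The document gives no baseline or change distribution, so the following are assumptions: normal baseline with SD 2, normal change, scores limited to 0–10, 2 million simulated participants per scenario. Responder rates:

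| Baseline mean | SD of change | True improvement | 18% of baseline | 1.8 points | 2 points |
|---|---|---|---|---|---|
| 5 | 2 | 0 | 33% | 17% | 15% |
| 5 | 2 | 1 point | 52% | 33% | 29% |
| 4 | 1.5 | 0 | 31–32% | 10% | 8% |

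The ranged entry depends on how a baseline of 0, where percentage change is undefined, is counted.

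- 18% of baseline against 2 points: 33 − 15 = 18, 52 − 29 = 23, and 31 or 32 − 8 = 23 to 24 percentage points.
- 1.8 points against 2 points: about 2 to 4 percentage points.
- In the first two rows, a true 1-point benefit raises the rate by 52 − 33 = 19 percentage points under 18% of baseline, and by 29 − 15 = 14 under 2 points.
- Share with baseline below 2: Φ((2 − 5)/2) = Φ(−1.5) ≈ 7% at mean 5; Φ((2 − 4)/2) = Φ(−1) ≈ 16% at mean 4.

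**4. Does the sample size show which rule was meant?** The total reproduces: 66 / 0.67 = 98.5, rounded up to 99 per arm, and 3 × 99 = 297. With 66 per group, 90% power and two-sided 1% (sidedness is not stated), a two-group t-test implies a standardised difference of 0.68. The implied SD is then:

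- 2 / 0.68 = 2.94 for a 2-point difference;
- 1.8 / 0.68 = 2.65 for 1.8 points;
- 0.9 / 0.68 = 1.32 for 18% of an assumed baseline of 5.

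The article gives no SD, so the calculation neither identifies the intended rule nor is contradicted by this point.

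**The case against.** The strongest reply is that the wording about baseline and follow-up may simply name the interval, and that the points gloss makes most sense as 18% of the scale, 1.8 or 1.98, rounded to 2. On that reading the gap is only about 2–4 percentage points. The rules are also nested: any 2-point fall meets both 18% readings. Because 18% recurs throughout and 2 points appears once, 18% is probably the operative figure. All of this stands, and it means that percentage of individual baseline is not established as the document's rule. It does not remove the problem, because the defining sentence still asserts an equality that fails and no section supplies the denominator.

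Stronger readings that a reader might infer are not supported:

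- **Worsening counts as success.** The statistical section speaks only of a change, but the Abstract, Primary objectives, Design and Outcome measures all say improvement, and the sample size paragraph says reduction.
- **The Primary objectives contain a third definition.** The mention of usual care there is most naturally the between-arm comparator placed inside the bracket. The real mismatch in that sentence is the strict inequality.
- **The threshold is being left until data are seen, or sits within measurement noise.** The document says neither and gives no measurement-error figure. An analysis plan may exist.
- **The lack of an NRS-S entry minimum is an error.** It is not. It only makes low baselines possible, and how they are handled is ordinary analysis-plan detail.

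**Conclusion.** The point holds: the primary endpoint's threshold is wrong as written, because 18% and 2 points are equated and are not equal, whether the 18% is taken of the individual's baseline or of the 0–10 range. That conclusion is arithmetic and needs no assumption.

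Its practical size depends on which reading of 18% was intended: about 2–4 percentage points in the responder rate if it is a share of the range, and about 18–24 if it is a share of the individual's baseline. Those sizes, and the 7–16% of participants who could never respond under the 2-point rule, rest on the assumed distributions above (baseline mean 4–5, SD 2; change SD 1.5–2; true effect 0–1 point). A reader might go on to infer that the 66 per group is miscalculated; nothing here shows that. Because the threshold decides who counts as a success in the confirmatory tests, it should be corrected before unblinding.

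**What to change.** Before unblinding:

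- State one rule for the primary endpoint: either a percentage of the individual's baseline or an absolute number of points on the 0–10 scale. Choose it to match the source the protocol cites for the minimal important difference. That source is not at hand, so this review does not select a value.
- Use one inequality, at least or more than.
- Delete the gloss that is not equivalent to the chosen rule.
- Apply the same wording in the Abstract, Primary objectives, Design, Outcome measures and Statistical analysis sections.
- Report the responder comparison under the other threshold as a sensitivity analysis.

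The cost is about one paragraph in the protocol or analysis plan and matching edits elsewhere. No additional data are needed, since both rules use the same 7-day means.
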